#### Analyses

Overall, the longitudinal data collection at baseline, 6 months, and 12 months following the inception of the trial will facilitate assessment of change over time and identification of factors that influence the outcomes. For the implementation outcomes, penetration will be analyzed by calculating the proportional change in number of low-income students participating in USM from prior to enacting the implementation strategy at baseline, 6 months, and 12 months following the start of the trial. For the costing measure, labor costs will be iteratively analyzed through the bottom-up approach to collect time and effort data from all implementing individuals; salary data will be obtained for all SDP positions through review of publicly available records. Receipts and invoices for all materials and miscellaneous costs will be analyzed. All costs will be calculated specific to each strategy to allow for accurate reporting and budget impact assessment showing net financial costs resulting from the strategies. The costconsequence analysis will be conducted to show the comparison of the costs and outcomes of each strategy in comparison to the waitlist condition (i.e., treatment as usual) [49, 72]. Data from the acceptability, feasibility, and sustainability surveys will be processed and aggregated at the school level to provide overall means. Interview data on other outcomes identified through the mapping procedure will be analyzed deductively through the GTE and Proctor outcomes framework [7, 57] followed by mapping ongoing determinants to the EPIS framework in the Implementation and Sustainment phases, providing tangible barriers and facilitators across the trial period [53]. This will enhance continuation of determinants analysis from Aim 1 and support adaptation/tailoring of the implementation strategies over time in response to needs/challenges at each school. Such adaptation is recommended by implementation science experts as a means to enhance equity through collaborations with community and clinical partners [43].

For the behavior/health outcomes, we will analyze data at baseline and 12 months to examine changes over time given that BMI, household food insecurity, and dietary behavior data are collected annually. Prior to analysis data will be cleaned following guidance from experts [73] and will entail checking for errors in the data such as incorrect, missing values, inconsistencies, and duplicates. We will work with the SDP Office of Research and Accountability to develop a cleaning plan and follow their best practices for data management including data security to maintain confidentiality. Datasets for each behavioral outcome will be created, to provide a school- and student-level dataset in R Software (Vienna, Austria). Exploratory hierarchical multiple regression models will be employed for each of the behavioral outcomes using students as the unit of observation and schools as the unit of analysis. Differences between intervention and control conditions will be determined, and school-specific effects, i.e., random effect for schools will be included in our models. This will allow correlations between students within schools which are nested within the intervention condition. We will also run regression models to examine change over time and what variables are associated with this change, examining trajectories among the intervention and comparison group. This will allow calculation of Intraclass Correlation Coefficient, providing necessary pilot data [74, 75] for a subsequent high-powered clustered trial.

The research team is well-equipped to support the monitoring of participants and schools in this study. We will take all precautions to address these discomforts, including training study staff to be aware of these potential issues and comfortable interacting with school personnel, parents, and adolescents. If participants seem uncomfortable or reactive to the study measures, they will have the option to discontinue data collection. Safety reports will also be created and sent to Temple University’s Data Safety and Monitoring Board (DSMB). Results of all assessments will be reviewed with the support of the mentorship team to determine whether subjects have experienced any adverse events. Any serious events, even though unlikely, will be reported within 24 h to Temple’s Institutional Review Board, as appropriate. If any protocol modifications occur, we will update the trial registration immediately.

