### Aim 1: use a community-engaged procedure to develop an equity-focused implementation strategy through a cluster randomized design

Informed by findings from the needs assessment (Task 1) [47], this aim will comprise identifying goals for implementation and objectives (Task 2), the development and tailoring of implementation strategies (Task 3), and implementation protocols (Task 4) for USM implementation through a cluster-randomized pilot design. From the schools in the needs assessment sample, two will be block randomized to receive implementation strategy selection support and two will implement USM as usual as a waitlist comparison group, before going through strategy development the following year (Fig. 2). Schools will not be blinded to this randomization given that they will be asked to sign a collaboration agreement and will be told whether they are completing mapping first or assigned to the waitlist condition. Eligible schools are those that have participated in our needs assessment or have agreed to collaboration through a formal agreement and are a public, non-charter school within the SDP.

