#### Recruitment and engagement

All schools who participated in Task 1 [47] will be re-engaged and invited to participate in the next phase of the project, with additional schools recruited in collaboration with our CAB and the district to secure a sample of 4 schools. We will ask all schools to sign a collaboration agreement (See additional file 1) that states they agree to be involved in the project to be randomized to the first pilot or the waitlist comparison condition. Once received, we will block randomize schools by pairing the sample (2 in each group) based on characteristics such as geographic location, size, mode of food service (i.e., satellite or full-service kitchen), and student/family demographics.

Grounded in the GTE and EPIS frameworks [7, 53], this implementation mapping aim will be completed with representatives (at least 3) and students from each of the 2 intervention schools. We will meet with pilot school principals early in the process to identify suitable individuals who are invested in the school meals program; necessary individuals to recruit are administrators (i.e., principals) and food service providers given their essential roles in steering meal provision practices. We will aim to recruit at least 1 student, parent, and teacher from each school through distributing flyers (See additional file 2) to schools and targeted sampling through the principal and other administrators to ensure we find individuals who are committed to the process and meetings. We will hold ~ 5 meetings during/after school (based on school team preference) roughly 3–4 weeks apart to accomplish Tasks 2–4 and prepare for full rollout. For all participants, we will distribute informed consent forms (and assent for students) to facilitate data collection and provide a $25 gift card per participant per meeting attended.

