#### Participants and procedures

Intervention school teams will receive coaching during the implementation phase with monthly check-in meetings at school sites or via phone/Zoom if necessary (~ 15–30 min) to support implementation efforts and retention of schools across the intervention period. Implementation leaders and other front-line implementers (i.e., food service staff) from intervention schools will be asked to complete surveys and brief interviews to address implementation outcomes. Administrators and food service providers will be asked to participate in interviews which will facilitate the development of the costing measure. Penetration and behavioral data for all 4 schools will be collected before Aim 1 begins and throughout study completion. Table 1 illustrates the implementation (in green) and behavior/health outcome (in blue) measures we will collect, the source, data collection period, and the timing/frequency of these measures for the hybrid type III implementation-effectiveness study.

**Table 1 Tab1:** Hybrid type III study: overview of variables, data source, collection period, and timing/frequency of data collection

	**Variable**	**Source**	**Data Collection Period**	**# Time Points/Frequency**
**Implementation Outcomes**	Penetration (Meal Participation)	Division of Food Services	Daily for Breakfast and Lunch	Monthly Average (%) per student
	Cost	Cost Survey and Interview	Fall and spring each year	4 (2 in each trial year)
	Acceptability	Implementation Survey	Fall and spring in first year	2
	Feasibility	Implementation Survey	Fall and spring in first year	2
	Sustainability	Implementation Survey	Fall and spring each year	4 (2 in each trial year)
	Implementation Determinants	Check-in Meetings	Monthly	18 (9 each year)
**Behavior/Health Outcomes**	Race, ethnicity, economic disadvantage	District database	Fall of each year	2
	Weight Status/BMI	Office of Health Services	Fall of each year	2
	Student hunger, self-reported participation, dietary behavior	Office of Research and Evaluation	Spring of each year (student survey)	2
	Attendance	District Database	Daily for each student	Monthly Average (%) per student

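### The 6- and 12-month penetration points have no single stated time origin, and a 6-month change from baseline compares different parts of the school year

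*Protocol article*

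**What the plan says.** The Aim 2 Analyses section opens with a general schedule: "longitudinal data collection at baseline, 6 months, and 12 months following the inception of the trial". For penetration it then calls for the relative change in how many low-income students take school meals, "from prior to enacting the implementation strategy at baseline, 6 months, and 12 months following the start of the trial".

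Under Aim 1, "two will be block randomized to receive implementation strategy selection support and two will implement USM as usual as a waitlist comparison group". Schools are therefore allocated before any strategy exists. Recruitment and engagement describes the mapping work: "We will hold ~ 5 meetings during/after school", "roughly 3–4 weeks apart to accomplish Tasks 2–4 and prepare for full rollout". Participants and procedures adds: "Penetration and behavioral data for all 4 schools will be collected before Aim 1 begins and throughout study completion". Table 1 records meals daily and summarises them as monthly averages, and it lists nine check-in meetings a year.

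**The concern.** The penetration sentence refers to two events, enactment of the strategy and the start of the trial, and the visible text does not say whether they coincide. If the trial starts at randomisation or with mapping, part of each follow-up window passes before there is a strategy to implement. Two analysts holding the same daily records could then compute different 6-month results for a primary outcome.

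A second problem does not depend on the first. School meals follow the school calendar. Any point six months after its baseline falls in a different part of the school year, or in a month without classes. The stated rule for penetration is a change from baseline, so a calendar shift within a school could pass for an effect or hide one. The pilot is meant to inform a larger cluster trial, and a mislabelled exposure time would carry into that design.

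**Working it through.** The plan gives no duration for mapping and no figure for time on strategy, so there is nothing to reproduce. The check has three parts.

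**1. What does *trial* mean in the article?**

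Places that support a trial including mapping:
- Background: the Aim 1 statement puts strategy development inside a cluster randomised trial.
- Methods, opening paragraph: only Task 1, the needs assessment, is said to come before the trial.
- Aim 1: randomisation is to strategy-selection support.
- Project timeline: the trial takes 3 years, whereas Aim 2 gives implementation 2 years. The waitlist year may explain part of this gap.

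Places that support a trial starting with Aim 2 implementation:
- Abstract, Methods: the hybrid trial belongs to Aim 2, the last mapping step.
- Aim 2, opening paragraph: it studies the trial's impact, with participation analysed over the implementation period.
- Table 1: there are two trial years, equal to the 2-year implementation period. Acceptability and feasibility of the strategy are surveyed from the fall of the first year.
- Participants and procedures with Table 1: check-ins belong to the implementation phase, and there are 9 in each year.

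The flow chart (Fig. 2) and the timeline (Table 2) may settle the matter, but they were not available for this check.

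**2. Time on strategy at each point, if the clock starts with mapping**

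Inputs: about 5 meetings, 3–4 weeks apart (Recruitment and engagement), and 365.25/12/7 = 4.348 weeks per month.

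- Mapping time = gaps × weeks per gap / 4.348
- Time on strategy at month *t* = *t* − mapping time
- Pre-exposure share = mapping time / *t*

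Five meetings have 4 gaps. A fifth gap, to allow for rollout preparation after the last meeting, is an assumption.

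| Gaps × weeks | Mapping | On strategy at month 6 | Pre-exposure share | On strategy at month 12 | Pre-exposure share |
|---|---|---|---|---|---|
| 4 × 3 = 12 | 2.76 months | 3.24 months | 46% | 9.24 months | 23% |
| 4 × 4 = 16 | 3.68 months | 2.32 months | 61% | 8.32 months | 31% |
| 5 × 3 = 15 | 3.45 months | 2.55 months | 57% | 8.55 months | 29% |
| 5 × 4 = 20 | 4.60 months | 1.40 months | 77% | 7.40 months | 38% |

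If the clock starts at rollout, time on strategy is 6 and 12 months and the pre-exposure share is zero.

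**3. Season and comparison**

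Baseline and a point six months later are half a calendar year apart whatever the origin. Nine check-ins a year are consistent with about nine active months, so a 6-month point can also fall out of session. For the behavioural outcomes, the Analyses section states differences between intervention and control conditions. For penetration it states only a change from baseline.

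**The case against.** The strongest objection is that nothing in the article says the trial starts when mapping starts. The penetration sentence can be read as one clock: baseline is just before enactment, so the start of the trial is enactment. Table 1 fits that reading well, because nine implementation-phase check-ins in the first year imply about a full school year of implementation. The figures that could decide the question were not available here, and their absence is no fault of the plan. This stands. It makes the exposure figures above conditional.

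A second objection is that season is partly handled by design. Meal data come from all four schools, before and throughout, and the waitlist schools are paired on location, size, food service and demographics, so calendar effects common to the district reach both arms. The cost-consequence analysis also sets outcomes against the waitlist condition. This stands in part. The data allow the contrast, but the rule written for penetration does not use it, and the cost-consequence sentence names neither penetration nor its time points.

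A third is that counting from allocation would be a legitimate as-randomised clock, since allocation is to selection support. That is true, but the article would then need to say so and give the time on strategy at each point.

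A reader might go further and infer that the 6-month result is mostly pre-exposure, that the 12-month result is presented as a one-year effect, or that a true rise would be roughly halved at month 6. The documents do not support these inferences. On the basic schedule the pre-exposure share is about half to three fifths on one reading and nil on the other. The article does not call the 12-month figure a one-year effect. Dilution would require averaging over all six months, whereas Table 1 gives monthly averages, and a single month-6 value would not be diluted in that way.

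**Conclusion.** The point holds as an unresolved time origin plus a seasonal mismatch. It does not hold as a demonstrated loss of exposure.

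- If the clock starts with mapping, and rollout follows the fifth meeting at once, month 6 carries about 2.3–3.2 months on strategy and month 12 about 8.3–9.2 calendar months. One further interval, an assumption, lowers these to 1.4–2.6 and 7.4–8.6 months.
- If the clock starts at rollout, nothing is lost.
- On both readings the 6-month change from baseline compares different parts of the school year or may fall out of session, and the rule for penetration states no contrast between arms.

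Because this concerns a primary implementation outcome and the remedy is cheap, the wording should be changed. It does not call the design or the data collection into question.

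**What to change.** Reconcile the passages by defining the start of the trial once, and separate it from the clock used for penetration:

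1. Set time zero as each intervention school's rollout date, and give its paired waitlist school the same date.
2. Define 6- and 12-month windows from that date, using in-session months only. Compare each with the same calendar months before rollout, in all four schools, and contrast the arms.
3. Report the mapping period separately as a preparation phase. The last 2.8–3.7 months before rollout are mapping months, so flag them where they serve as the reference for the end of the 12-month window.
4. Close the last window before the waitlist schools' own rollout. If their mapping starts 12 months after that of the intervention schools and takes equally long (both assumptions), their rollout comes 12 months after the intervention rollout, so a 12-calendar-month window just fits.
5. BMI, food insecurity and diet are measured once a year and cannot be re-anchored. Report time on strategy at measurement for each. For BMI the season must first be reconciled: Table 1 gives fall, and Data sources and secondary outcomes gives spring.

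The cost is mainly protocol wording. Daily meal records linked to student ID are already obtained. The one likely addition is a prior-year extract in the district data request.

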#### Data collection procedures and measures

We will utilize predominantly qualitative methods for this strategy development aim through a series of semi-structured meetings with school representatives. Each planning meeting will accomplish part of a mapping task (Tasks 2–4); workbooks will be developed by the research team to distribute to all attendees to facilitate discussion. These workbooks will be developed through review of prior examples of successful toolkits for implementation strategy development [60] in collaboration with our CAB and the school district. Meetings for Task 2 (identify outcomes) will focus on reviewing data from Task 1 (needs assessment), getting feedback from school representatives on findings, and setting goals for implementation. Example prompts will include: “What findings shocked you or stood out?” and “what do you want to see change with the school meals program?” to arrive at clear goals and desired improvements for the program.

Meetings for Task 3 (develop strategies) will focus on taking the desired goals and objectives and developing strategies for improving implementation. We will facilitate refining ideas and asking representatives to collectively rate the difficulty and complexity of chosen strategies (i.e., easy, moderate, hard) and cite potential barriers to implementation. Example prompts for discussion include: “What strategies or practices do you think we could try to address some of these challenges to school meals?” and “What barriers would we need to consider for implementing this strategy?”. Finally for Task 4 (develop protocols) we will collectively finalize the chosen strategies and begin to “backwards plan” for these by discussing what materials/supplies, funding, training, and other support is needed to execute these strategies (prompt: “what do we need to implement this strategy?”) and to decide on the timing, intensity, and frequency of implementing them. Example prompts include: “What funding do we need to get this strategy/project implemented?” and “How often/much are we going to do this [strategy]” for each of the strategies the group selects to test out. We will also discuss who will lead the deployment of each strategy. This will facilitate creation of protocols in alignment with reporting recommendations for implementation strategies [61]. We will record all meetings and have them professionally transcribed verbatim.

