#### Data collection and primary outcomes

The number of breakfast and lunch meals served (linked to student ID) will provide data on penetration, facilitating assessment of equitable access to low-income students. For cost of implementation, Our team will develop a bottom-up costing strategy and measure the costs for each implementation strategy that results from the mapping process, following guidance from experts in economic evaluation of implementation [49, 66] and in collaboration with our CAB and school district partners. We will do this by establishing categories of resource use for each strategy (e.g., labor, materials, travel) and developing initial measures to capture time and effort of all implementing participants at the school sites. We will then conduct a budget impact analysis and costconsequence analysis to enhance understanding of the value for each strategy and determine potential for scale-up. Validated surveys adapted for the school context by the principal investigator (see additional file 3) will provide data on acceptability, feasibility, and sustainability of the implementation strategy by each member of the implementation team [67–69]. Finally, brief (i.e., 20–30 min) interviews will be held with key implementing representatives (identified in Task 1) to identify the degree to which implementation objectives were met grounded in the GTE toward the end of the first year of implementation [38, 44, 45]. We will also ask about overarching facilitators and barriers during these interviews, mapping determinants to the Implementation and Sustainment phases of EPIS. To support replicability of our protocol, all surveys, interview guides, coding materials, and other pertinent documents will be made publicly available on our lab website and through article publication.

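### The cost-consequence analysis promises outcomes of each strategy against waitlist, but the design supports student-outcome contrasts only for each school's whole package

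*Protocol article*

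**What the plan says.** The Aim 2 Analyses section of the protocol article states that the cost-consequence analysis will "show the comparison of the costs and outcomes of each strategy in comparison to the waitlist condition". The section Data collection and primary outcomes gives the purpose: to "enhance understanding of the value for each strategy and determine potential for scale-up". On the cost side the plan is explicit and workable: "All costs will be calculated specific to each strategy".

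The design is set out under Aim 1. Of four schools, "two will be block randomized to receive implementation strategy selection support and two will implement USM as usual as a waitlist comparison group". The waitlist schools go through strategy development a year later.

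Strategies are chosen afterwards, by the school teams. In Aim 1, Data collection procedures and measures, resources and frequency are to be discussed "for each of the strategies the group selects to test out". The same section says "we will collectively finalize the chosen strategies" and that the group is "to decide on the timing, intensity, and frequency of implementing them". The Aim 2 Analyses section adds "adaptation/tailoring of the implementation strategies over time in response to needs/challenges at each school".

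The only between-group contrast specified there, for the behaviour and health outcomes, is intervention against control with a random effect for school.

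**The concern.** The cost half and the outcome half of the comparison are available at different levels. Time, labour and invoices can be booked to a strategy. A change in meal participation, food insecurity, diet or BMI arises in a school that has received mapping support, coaching and whatever strategies its team selected. Nothing in the design separates those components from one another.

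If the table is built as described, each strategy's row would carry an outcome difference against waitlist that belongs to the whole package. The protocol intends to use the result to judge value and potential for scale-up, and in several places names cost as a primary implementation outcome. A reader could then take one strategy forward on evidence that concerns only the combination.

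**Working it through.** The protocol gives no figure to reproduce. The question is whether a strategy's own effect against waitlist can be identified.

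**Inputs.** Four schools, two per arm, paired before randomisation (Aim 1; Recruitment and engagement). Strategies are chosen by each team, in the plural, with their number not fixed (Aim 1, Data collection procedures and measures). No factorial assignment, planned staggering or record of individual students' exposure to particular strategies is described.

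**Model.** For school s, write the change as y_s = μ + Σ_j β_j x_sj + e_s. Here x_sj = 1 if school s uses strategy j, and 0 for every j in the waitlist schools. The effect β_j is estimable only if its unit vector lies in the row space of the design matrix. The two waitlist rows are identical, so there are at most three distinct rows and the rank cannot exceed 3.

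**Results for assumed patterns** (letters are strategies; the two intervention schools are separated by a slash):

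| Pattern | Parameters | Rank | Residual df | Strategy effects estimable |
|---|---|---|---|---|
| A / A | 2 | 2 | 2 | A, identical to the arm effect |
| A / B | 3 | 3 | 1 | both, each resting on one school |
| AB / A | 3 | 3 | 1 | both, each resting on one school's choice |
| AB / AB | 3 | 2 | 2 | none |
| ABC / ABC | 4 | 2 | 2 | none |
| AB / AC | 4 | 3 | 1 | none |
| AB / CD | 5 | 3 | 1 | none |
| ABC / ABD | 5 | 3 | 1 | none |

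**General rule.** The row space beyond the intercept is spanned by the two schools' 0/1 strategy vectors, b1 and b2. The unit vector for j lies in that span only if one school runs j alone (b1 or b2 equals it) or the two packages differ by j alone (b1 − b2 equals it up to sign). So AB / ABC would yield C, but only as the difference between two intervention schools. That is not a randomised contrast, and A and B stay inseparable.

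**The algebraic exceptions.** With 1 residual df the two-sided 5% t critical value is 12.7. More importantly, strategy and school coincide, so a school's own trend cannot be told from the strategy's effect. In A / A the estimate is the arm effect, which still includes mapping and coaching.

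**Package level.** One arm effect plus an intercept gives rank 2 for 2 parameters: estimable, with 2 residual df (t critical value 4.30). With two matched pairs there are 2² = 4 assignments, so the smallest two-sided randomisation p is 2/4 = 0.50. Unpaired, there are 6 assignments and it is 2/6 = 0.33. The package contrast is identified, but with four schools it can only be descriptive.

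**Implementation outcomes.** Under Participants and procedures, implementation surveys and interviews are sought from intervention schools. Under Aim 2 Analyses, the acceptability, feasibility and sustainability surveys are averaged by school. They have no waitlist value to be compared with.

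**The case against.** Four points deserve weight.

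- **Simultaneous deployment is not stated.** A reader might infer that all of a school's strategies run over the same period. The protocol leaves timing to the teams, so roll-out could be staggered. This stands, and the point must not rest on concurrency. But no staggering is planned, and unrandomised staggering within two schools would be confounded with calendar time and carry-over.
- **The number of strategies is open.** The Background, the theoretical framework section and parts of Aim 2 speak of a single strategy. If both schools used one common strategy, strategy and arm would coincide and the problem would disappear. The sections that plan the costing, however, use the plural.
- **Some outcomes can be tied to a strategy.** A reader might infer that no outcome at all can be. That is too strong: the opening of Aim 2 words acceptability, feasibility and sustainability at the level of a strategy, and these could be described strategy by strategy. What they lack is a waitlist comparison. Meals are also recorded daily by student, but without student-level exposure to individual strategies this does not separate them.
- **This is a pilot, and cost-consequence analysis is descriptive.** No ranking of strategies and no cost-effectiveness ratio is planned, which limits the harm. A reader might try to put a multiple on the distortion. The documents give no number of strategies, size of gain or rule for crediting it, so none can be derived.

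Leaving detail to an analysis plan is no answer. The difficulty is a stated comparison that the design cannot supply, and later detail cannot create it.

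**Conclusion.** The point holds for the student outcomes. Unless each intervention school uses only one strategy, differences from waitlist in meal participation, food insecurity, diet or BMI can be attributed only to that school's package. With one different strategy per school, or nested packages, an estimate exists algebraically but strategy is confounded with school. The per-strategy outcome comparison against waitlist is therefore invalid as written, while the per-strategy costing is sound.

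The conclusion assumes more than one strategy in at least one intervention school, or different strategies between the two, as the plural wording suggests. It does not depend on any power, alpha or effect-size figure, and it does not require that strategies run simultaneously. Its size is one of identifiability rather than of bias: in every tested pattern where the schools have two or three strategies each, no strategy effect is estimable. It should be corrected, since the result is intended for scale-up decisions.

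**What to change.** Amend two places in the protocol article: Data collection and primary outcomes, and the Aim 2 Analyses section.

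- Keep the itemised costs per strategy, and present those rows as cost only.
- Set participation and health consequences against the total cost of the package, by school and by arm, as intervention minus waitlist. Restrict this to the period before the waitlist schools begin their own strategy development, and state which dates those are.
- State that the comparison is descriptive, given four schools.
- If acceptability, feasibility and sustainability are reported by strategy, label them as intervention-school descriptions without a waitlist contrast.
- Limit statements on value and scale-up to mapping plus the resulting package.

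The cost is wording and table layout; no new data are needed. What is given up is a per-strategy value comparison on student outcomes, which this design could not have provided.
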